### Frequency and plans for auditing trial conduct {23}

The trial will be audited independently by investigators from the Clinical Trials Office at Karolinska University Hospital who will perform monitoring on-site or remotely according to good clinical practice (GCP) and national regulations.

### Plans for communicating important protocol amendments to relevant parties (e.g., trial participants, ethical committees) {25}

In the case changes in the protocol are necessary, relevant amendments will be made and submitted to the relevant ethics trial registration authorities and a resubmission with amendments to the study protocol will be submitted to Trials. All participants will provide informed written consent prior to their entry into the study.

### Dissemination plans {31a}

Results from the study will be published in scientific journals and popular science summaries will be sent to relevant patient organizations for dissemination. Results will be presented at international congresses and in the clinic and will also be communicated directly to and through the organizations that are responsible for developing and disseminating information on the National Physical Activity Guidelines and the Exercise Guidelines for the Prevention and treatment of Disease (FYSS textbook).

## Discussion

Developing countermeasures that deter muscle wasting in response to cancer could lead to major advances in improving the quality of life and extending survival in patients with upper GI and hepatobiliary cancers. Specifically, findings that will be generated from this study will lead to a better understanding of the skeletal muscle molecular characteristics in these fragile patient populations and shed light on the effects of BFR-T on skeletal muscle responses which is currently not understood. In fact, a major constraint in the development of therapies and countermeasures to prevent muscle wasting is the limited knowledge of the underlying mechanisms of cachexia derived from human studies, in large part due to the challenges of obtaining tissue samples from patients with cancer. The present study incorporates a novel approach in the cancer setting to counteract muscle atrophy through the incorporation of blood flow-restricted resistance training in the perioperative setting for patients with resectable pancreatic, biliary tract, and liver cancer.

Due to the COVID-19 pandemic, the study start was delayed for almost 1 year. The initial plan was to include a more homogenous group: patients diagnosed with pancreatic or biliary tract cancer undergoing a pancreaticoduodenectomy; however, there were major challenges with the inclusion rate resulting in the study taking longer and risking a loss of statistical power. Amendments were made to the original plan to expand the inclusion criteria to patients undergoing either pancreaticoduodenectomy or laparoscopic surgery and to also patients with malignancies in the liver amendable for surgical resection. These changes were approved by the Swedish Ethical Review Authority and the Norwegian Regional committees for medical and health research ethics. We are aware that this will result in a heterogeneous group of patients. There is considerably less risk of complications for patients undergoing laparoscopic surgery compared to a pancreaticoduodenectomy; however, these potential differences will be adjusted for in the statistical analysis. Moreover, time to surgery and post-surgery recovery are similar across the diagnoses. In this study, we decided to include any patient who is diagnosed with resectable pancreatic, biliary tract, or liver cancer regardless of time-to-surgery which means that some patients will only have time to perform (T0) before surgery, while some will perform both (T0) and (T1). In some cases, time-to-surgery is only a few days which means that inclusion is not possible at (T0) but will instead take place at (T2). The reason for including patients at (T2) is that time-to-surgery is significantly shorter at the Norwegian site; consequently, amendments to the original plan had to be made to accommodate for the reduced time-to-surgery. We will perform a subgroup analysis to evaluate the rehabilitation effect (T2 to T3). Other amendments to the original plan include the addition of digitally supervised exercise and an exercise diary to be able to monitor exercise adherence more efficiently.

We anticipate that adaptations to the exercise program will be required since these patient populations have a high disease burden and fluctuating health and performance status. Regular monitoring of the patients’ health status will be performed to adapt and personalize the exercise prescription. This means that the prescribed cuff pressure may decrease based on the self-reported rating of perceived exertion and the exercises may vary slightly based on post-surgery restrictions or complications. We believe that such adaptations to the initial planned training schedule are necessary for these specific populations.

To enhance adherence to the exercise regimen, the exercise sessions are personalized and home-based to avoid travel which has been shown to be a major barrier to exercise [23]. Additionally, utilizing a home-based training approach could offer a safer alternative for these patient populations, given their heightened susceptibility to infections. It is imperative for them to steer clear of infections to ensure timely eligibility for surgery.

In exercise-oncology trials, contamination is reported in 37% of cases. To mitigate this risk, we have implemented recommended measures, such as offering general exercise guidance along with an activity tracker to the control group [24]. While providing the activity tracker may potentially increase the physical activity levels of controls, research indicates that such proactive measures reduce the likelihood of drop-out and contamination [24].

In conclusion, in the PREV-Ex exercise trial, we are investigating the effects of blood flow-restricted resistance training in patients with pancreatic, biliary tract, and liver cancer in the perioperative setting on muscle thickness and muscle cross-sectional area, physical fitness, body composition, patient-reported and objective health-related outcomes, hospitalization, blood status, and skeletal muscle molecular characteristics. Findings from the study will shed light on the potential of a personalized exercise approach to act as a powerful strategy to counteract cancer-related muscle wasting. It will pave the way for the evidence-based practice that is needed to embed exercise into routine care for patients that are in crucial need for a strategy that can slow down the rate of skeletal muscle deterioration.

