
### Objectives {7}

The *overall objective* of this randomized controlled trial is to examine if low load BFR-T can prevent muscle atrophy or mitigate its progression by studying changes in muscle mass and muscle signaling in patients with resectable pancreatic, biliary tract, or liver cancer.

Using a two-armed randomized controlled trial *the primary aim* of this project is to assess if a BFR-T program can preserve or increase skeletal muscle mass measured as thickness and cross-sectional area in patients with resectable pancreatic, biliary tract, or liver cancer.

The *secondary aims* are to investigate the effects of BRF-T on:Myogenic stem cells, mitochondrial function, capillarization, macrophage infiltration, and muscle catabolism, measured in skeletal muscle biopsies from a subgroup of voluntary participantsMuscle strength, physical function, body composition, and physical activity levelsSelf-reported fatigue, health-related quality of life (HRQoL), and nutritional statusThe patients’ experience of the exercise programHospitalization, prognostic markers, and different blood status concentrations

The use of BFR-T using low training loads may allow for a quick postoperative recovery by avoiding the high levels of mechanical muscle stress typically associated with high-load resistance exercise. Thus, BFR-T could serve as a feasible exercise modality in this patient population to mitigate the burden of cachexia. Moreover, the metabolic stress induced by BFR-T may have the potential to normalize the disrupted intramuscular milieu in cachectic muscle leading to a proper muscle regenerative response. Therefore, it is expected that the challenge imposed by BFR-T will:Stimulate muscle hypertrophy and thereby preserve or increase muscle massInduce beneficial effects on skeletal muscle characteristics in terms of myogenic stem cell count and differentiation, basal autophagy activity, mitophagy/biogenesis, capillaries per muscle fiber, macrophage infiltration, and reduce the levels of catabolic markersImprove muscle strength, physical function, and physical activity levelsCounteract an increase in self-reported fatigue and a decline in HRQoLDue to its proposed positive effects on skeletal muscle mass and quality, lead to lower hospitalization rates

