### Trial design {8}

This Prev-Ex is a multi-center, two-armed randomized controlled trial (RCT) with 1:1 allocation ratio, stratified for research site, and testing the superiority of the intervention. Patients diagnosed with resectable pancreatic, biliary tract, and liver cancer are randomized to an exercise program consisting of home-based low-load BFR-T during both a pre- and postoperative period consisting of a total of 6–10 weeks, or a control group. Besides the nutritional support offered as standard care for these patients, protein supplementation will be given to both groups to ensure adequate protein intake. See Fig. 1 for the modified SPIRIT study flow chart.

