## Statistical methods

### Statistical methods for primary and secondary outcomes {20a}

Data will be analyzed using the IBM SPSS (Statistical Package for the Social Sciences) 26 statistical package for Windows (SPSS, Chicago, IL, USA). For the quantitative analysis, descriptive statistics, ANOVA, and chi-squared tests will be used to describe and compare baseline characteristics. For longitudinal analysis, linear mixed modeling adjusted for baseline values (T0) of the outcome will be used to detect any significant differences between the two groups from pre- to post-intervention as well as at follow-up 6 months following surgery. Group-by-time interaction will be included as a fixed effect. Corresponding effect sizes will also be calculated. Chi-squared tests and corresponding odds ratios will be calculated for hospitalization rates. All tests will be 2-tailed and statistical significance set at *p* ≤ 0.05.

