### Methods for additional analyses (e.g., subgroup analyses) {20b}

For the primary outcome the model will, besides being adjusted for the baseline value, also be adjusted for diagnosis and type of surgery. Per protocol analysis for those who have adhered to the exercise program will be performed. Potential moderators of the exercise effect will be explored (e.g., age, sex, type of surgery, diagnosis). In addition, mediation analyses will be performed to explore potential underlying mechanisms of exercise effects (e.g., blood and muscle biomarkers). A subgroup analysis will also be performed to assess the rehabilitation effect only considering that some patients have a very limited time to exercise prior to surgery or may not be included until T2 due to very short time-to-surgery.

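### The assurance that surgical differences will be adjusted for is carried out only for the primary outcome; the secondary mixed models and the hospitalization test leave surgery type out

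*Protocol article*

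**What the plan says.** Four places in the protocol article bear on this.

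- **Discussion.** After describing the expansion of eligibility, the text concedes that the group is heterogeneous and states: "There is considerably less risk of complications for patients undergoing laparoscopic surgery compared to a pancreaticoduodenectomy". Its statistical answer is "however, these potential differences will be adjusted for in the statistical analysis". No outcome is named and none is excluded.
- **Methods for additional analyses {20b}.** "For the primary outcome the model will, besides being adjusted for the baseline value, also be adjusted for diagnosis and type of surgery". This is the only place where surgery type or diagnosis is made a covariate. The same section lists both as potential moderators to be explored.
- **Statistical methods for primary and secondary outcomes {20a}.** For the longitudinal outcomes, "linear mixed modeling adjusted for baseline values (T0) of the outcome will be used". For hospitalization, "Chi-squared tests and corresponding odds ratios will be calculated for hospitalization rates".
- **Trial design {8}.** Allocation is "with 1:1 allocation ratio, stratified for research site". Neither operation nor diagnosis is a stratification factor.

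Hospitalization is a listed secondary outcome. The Objectives section expects the training to "lead to lower hospitalization rates".

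**The concern.** The Discussion uses adjustment as its answer to the heterogeneity created by the amended eligibility. A reader would take that to cover any outcome sensitive to the type of operation. The methods limit it to muscle thickness and cross-sectional area.

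The reason given for adjusting is complication risk. Complications are not a listed outcome, but hospitalization is, and it is plausibly the listed outcome that complication risk affects most. That is a judgement; the protocol does not define hospitalization in terms of complications.

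With 26 patients per arm and no stratification by operation, chance can put noticeably more of the higher-risk operations in one arm. An unadjusted difference in hospitalization would then partly reflect the surgery mix. If the covariate set for secondary outcomes stays unsettled, the choice between adjusted and unadjusted results could also be made after the data are seen, in a trial where investigators and most outcome assessors are unblinded.

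**Working it through.** **1. The text.** The mismatch needs no arithmetic. The Discussion's assurance is unrestricted; section {20b} restricts the covariates to the primary outcome; section {20a} fixes baseline-only models and a plain chi-squared test. Exploring surgery type as a moderator asks whether the exercise effect differs by operation. It does not adjust the between-arm comparison. The protocol gives no figure on this point to reproduce.

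**2. How often the arms would differ.** From the protocol: 52 patients, 26 per arm. Assumed: the number K of pancreaticoduodenectomies. Site stratification and blocking are ignored. The number X in one arm is hypergeometric, and the gap between arms is G = 2X - K.

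For K = 26, SD(G) = 2 x sqrt(26 x 0.5 x 0.5 x 26/51) = 3.64.

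| K of 52 (assumed) | P(gap of 6 or more, either direction) | One direction (half) |
|---|---|---|
| 26 | 16.5% | 8.2% |
| 16 or 36 | 13.2% | 6.6% |
| 10 | 7.5% | 3.8% |
| 13 | 5.2% | 2.6% |

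G is odd when K is odd, so for K = 13 the smallest gap that counts is 7. The range is about 5-17% in either direction and 3-8% in one direction.

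**3. What such a gap does to hospitalization when treatment has no effect.** Shift in risk difference = (G/26) x (risk after pancreaticoduodenectomy - risk after laparoscopic surgery). The protocol gives no rates. With 40% and 10% assumed, a gap of 6 gives 6/26 x 0.30 = 0.069, or 7 percentage points. For a 20-point difference in surgery mix, assumed rates of 35% v 15% give a shift of 4 points (odds ratio 1.24), and 60% v 20% give 8 points (odds ratio 1.40).

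**4. Rejection of a true null at two-sided 5%, by simulation.** N = 52, K = 26 (assumed). For this split, a gap of 6 or more is the same as a difference of at least 20 points in surgery mix, because possible gaps are even (4/26 = 15 points, 6/26 = 23 points).

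| Assumed hospitalization, laparoscopic v pancreaticoduodenectomy | Chi-squared, all trials | Mantel-Haenszel, all trials | Chi-squared, gap of 6 or more | Mantel-Haenszel, gap of 6 or more |
|---|---|---|---|---|
| 15% v 35% | 5.8% | 5.1% | 7.5% | 5.0% |
| 10% v 40% | 5.5% | 4.9% | 9.3% | 5.0% |
| 15% v 50% | 5.5% | 5.0% | 10.4% | 5.0% |
| 20% v 60% | 5.4% | 4.8% | 10.9% | 5.0% |

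A wider contrast (15% v 60%) brings the chi-squared figure in imbalanced trials to about 12%. A narrow one (20% v 35%) brings it to about 6%.

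**5. Power for hospitalization.** At an assumed odds ratio of 0.25, chi-squared v Mantel-Haenszel gives 40.2% v 38.5% (15% v 35%), 45.1% v 45.8% (15% v 50%) and 49.3% v 51.9% (20% v 60%). The change runs from -2 to +3 points, which is no consistent gain.

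**6. Continuous secondary outcomes.** If surgery and diagnosis explain a share R2 of the variance left after baseline adjustment, omitting them multiplies the standard error by 1/sqrt(1 - R2): 1.05, 1.12 and 1.20 for R2 = 0.1, 0.2 and 0.3. These R2 values are assumptions, and the true share beyond baseline may be smaller.

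**The case against.** The strongest reply is that there is no strict contradiction. The assurance is one sentence in a Discussion, it does not promise adjustment of every outcome, and section {20b} carries it out for the outcome on which the trial was sized. Covariates for secondary outcomes are often left to an analysis plan. Part of this stands: the primary outcome has the safeguard. But the protocol is not silent about the rest. It names the hospitalization test and ties the covariates to the primary outcome, so an analysis plan that adjusted the secondary outcomes would go beyond what these sections state.

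A second reply is that an unadjusted randomized comparison is valid and that stratifying gains little. This stands in full. A reader might infer that the chi-squared test is biased or invalid; across all randomizations its type I error stays at about 5-6%. A reader might also infer that serious imbalance is likely. It is not: about 5-17%, and only 3-8% in the direction that would favour the exercise arm. The upper figure needs an equal split, which the protocol does not state, and the eligible population also includes liver resections.

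A third reply is that adjusting every secondary model is unworkable for biopsy outcomes, which come from volunteers at the Norwegian site only. This also stands, and the fix leaves them out.

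**Conclusion.** The point holds as a mismatch between an unrestricted assurance and methods that honour it only for the primary outcome. Its practical size is modest. Overall error control is sound, and the exposure is confined to trials where chance puts 6 or more extra pancreaticoduodenectomies in one arm. In those, the hospitalization test rejects a true null in about 7-12% of cases, against 5% when stratified by surgery. These figures rest on an assumed surgery mix and assumed hospitalization rates, since the protocol gives neither.

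It would go too far to say that the safeguard is missing where it matters most, or that the trial's main conclusion is at risk: the primary model already includes both covariates. Nor do the calculations support a claim that power for hospitalization is being lost. Severity is low, because only secondary outcomes are affected.

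**What to change.** Use the covariates of section {20b}, namely diagnosis and planned operation as recorded before randomization, in the mixed models for the secondary outcomes measured in the full sample. Leave out the Norwegian biopsy subset. Replace the plain chi-squared test for hospitalization by a Mantel-Haenszel test and odds ratio stratified by planned operation. Fix this before the outcome data are analysed.

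If the sponsor prefers the present analyses, the alternative is to limit the Discussion sentence to the primary outcome and to say that secondary outcomes are adjusted for baseline only and hospitalization is unadjusted.

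The cost is a change of wording and a few degrees of freedom in the mixed models. The covariates are already needed for the primary analysis. Strata with few hospitalizations will add little information to the stratified test.

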## Trial status

Protocol version number: 1.1 dated March 12, 2024.

Date when recruitment began: May 2022.

Date when recruitment is expected to be completed: November 1, 2024.

## Data Availability

The principal investigator archives the screening and inclusion log and other documents, such as informed consent, in a secure, fireproof cabinet marked as strictly confidential. All data will be stored at the local study center in an electronic logbook at Karolinska Institutet (KI ELN). Coded personal data can be stored in KI ELN since access to the data is limited to specifically authorized persons and the audit trail enables tracing of who viewed the results and when.

## Abbreviations

AE: Adverse event
ANOVA: Analysis of variance
BFR-T: Blood flow restriction training
UC: Usual care
CT: Computed tomography
DMC: Data monitoring committee
ECOG: Eastern Cooperative Oncology Group
EORTC: European Organization for Research and Treatment of Cancer
GCP: Good clinical practice
HRQoL: Health-related quality of life
PG-SGA: Patient-Generated Subjective Global Assessment scale
RCT: Randomized controlled trial
SAE: Serious adverse event
AOP: Arterial occlusion pressure
